7.1.2. Experimental treatment arm (TS-1-treated arm)

1) Treatment regimen

TS-1 will be administered by the oral route daily for 14 days (Day 1-14) with a 7 day rest period (Day 15-21). The daily dose (80 mg, 100 mg, or 120 mg), which is based on body surface, will be divided into 2 doses daily (after breakfast and dinner) This 21-day (3-week) period will comprise 1 cycle and will be repeated for 1 year from the protocol treatment initiation day (about 18 cycles will be administered). New cycles will not be started after 1 year has elapsed from the protocol treatment initiation date. After completion of UFT treatment, subjects will be followed for up to 5 years (for 3 years after enrollment of the last subject), and antineoplastic therapy will not be performed until metastases or relapse are confirmed.

Daily oral TS-1 treatment for 14 days

7-day rest period

Day 1 Day 14 Day 21

TS-1 dose and administration method

| Body surface area | Single dose at treatment  initiation (FT equivalent) | Daily dose  (FT equivalent) | Breakfast | Lunch | Dinner |
| --- | --- | --- | --- | --- | --- |
| < 1.25 m^2^ | 40 mg/dose | 80 mg | 40 mg | - | 40 mg |
| ≥ 1.25 m^2^ to <1.5 m^2^ | 50 mg/dose | 100 mg | 50 mg | - | 50 mg |
| ≥ 1.5 m^2^ | 60 mg/dose | 120 mg | 60 mg | - | 60 mg |

2) TS-1 specifications

TS-1 Capsules 20: 20 mg FT equivalent per capsule

TS-1 Capsules 25: 25 mg FT equivalent per capsule

7.2. Criteria for changing dose and schedule (Rest days or reduced dose days will be recorded in the chart without fail.)

The following terminology will be used for change criteria.

Rest: A temporary holiday during which drug is not administered during the protocol treatment dosing period after which treatment can be resumed if the conditions are satisfied.

Dose reduction: Administration of less than the specified dose

Discontinuation: The protocol treatment is discontinued, and treatment will not be resumed during the subject’s participation in the study.

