7.2.1. Rest criteria and resumption criteria

When starting a TS-1 cycle (after the rest period from the previous cycle) and when performing tests during UFT treatment, it will be confirmed that all test values satisfy the dosing criteria before resuming treatment. When the dosing criteria are not satisfied, treatment will be withdrawn and resumed according to the following criteria.

1) Rest criteria

If the following adverse events which apply to the rest criteria occur during the drug treatment period, drug treatment will be immediately withdrawn, the (sub)investigator will wait until the values return to at least the treatment resumption criteria before resuming treatment.

The (sub)investigator will decide whether or not to withdraw treatment when rest criteria apply to the laboratory values of subjects whose baseline values are close to the rest criteria.

Rest criteria *Non-hematologic toxicities: Adverse events from sections of the CTCAE other than Blood/Bone Marrow

| Parameter | | Criterion for prescribing rest |
| --- | --- | --- |
| Hematologic toxicities | WBC | < 3,000 /mm^3^ |
|  | Neut | < 1,500 /mm^3^ |
|  | PLT | < 75,000 /mm^3^ |
|  | Hb | < 9.0 g/dL |
| Non-hematologic toxicities  * | T.Bil | ≥ 2.0 mg/dL |
|  | AST⋅ALT | ≥ 100 IU/L |
|  | Cr | ≥ 1.2 mg/dL |
|  | Other adverse events | ≥ Grade 2 |
| Other instances in which the investigator determines that rest is necessary because of adverse events, etc., in order to continue the protocol treatment. | | |

2) Treatment resumption criteria

(1) UFT-treated arm

After withdrawing treatment, the investigator will wait until the treatment resumption parameters return to normal to resume treatment. The dose at treatment resumption will be determined in accordance with the dose reduction criteria (refer to 7.2.2.). When the rest period exceeds 28 days due to adverse events, the subject’s protocol treatment will be discontinued.

(2) TS-1-treated arm

After a rest of at least 1 week in the TS-1-treated arm, it will be confirmed that the following treatment resumption criteria have been satisfied before resuming TS-1 treatment. The dose at treatment resumption will be determined in accordance with the dose reduction criteria (refer to 7.2.2.). When the rest period exceeds 28 days due to adverse events, the subject’s protocol treatment will be discontinued.

Example) When rest starts on Day 8 of the first cycle

after at least 1 week of rest, it is confirmed if treatment can be resumed.

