9.1.2. During the study period

1) Testing dates

(1)TS-1-treated arm (experimental treatment arm)

The observations and tests listed below will be performed on the first dosing day (Day 1) and Day 8 of the first cycle and on the first day of the second and all subsequent cycles. The results will be entered in the case report forms via the web at the fourth and eighth cycles and at completion of treatment after 1 year.

(2)UFT-treated arm (control treatment arm)

The observations and tests listed below will be performed on the first dosing day (Day 1), Day 8, and Day 29 during the first 4 weeks and then every 4 weeks, starting at Week 5. The results will be entered in the case report forms via the web at 3, 6, and 12 months (completion of treatment).

2) Observations and tests: The following tests will be performed on the prescribed testing days.

Note that only the underlined data below will be reported via the web.

ECOG performance status scale: PS

Test parameters related to the study drugs

Compliance*: Compliance will be confirmed based on the medication record and scored on the following scale. The investigator will score compliance on the following 4-grade scale every 4 cycles for TS-1 and every 3 month for UFT.

*The percentage of drug taken during the dosing period will be calculated. Note that the number of capsules not taken during the rest period will not be included in the calculation.

(1) Took 100% (2) Took ≥ 75% and < 100%, (3) Took ≥ 50% and < 75%, (4) Took < 50%

Rest: presence of rest, reason for rest,

duration of rest (rest initiation date and treatment resumption date)

Dose reduction: presence of dose reduction, reason for dose reduction, daily dose after reduction

Discontinuation: presence of discontinuation, discontinuation date, reason for discontinuation

Submission of follow-up data after withdrawal of consent: possible, not possible

Clinical laboratory tests

Hematology: WBC, Neut, PLT, Hb

Blood biochemistry: T.Bil, AST, ALT, Cr, LDH*, ALP*, CRP*, Na*, K*, Cl*, Ca*

*Will be done when possible

(Only WBC, Neut, PLT, Hb, T.Bil, AST, ALT, and Cr will be entered in the record; the presence of adverse events in each test and the highest grade will be entered.)

Tumor markers: SCC or CYFRA

(Will be measured if necessary. Results will be entered via the web if measured within 30 days before or after discontinuation or completion of protocol treatment.)

Adverse events

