9.2. Observation, test, and reporting schedule

∙Observations and tests (there will be a testing window of ± 14 days starting at Treatment Week 4 and ± 28 days during follow-up.)

| Time performed  Test | Enrollment | Treatment period | | | | | | | Discontinuation | Treatment completion | Follow-up † | Completion of follow-up |
| --- | --- | --- | --- | --- | --- | --- | --- | --- | --- | --- | --- | --- |
|  |  | TS-1-treated arm | | | UFT-treated arm | | | |  |  |  |  |
|  |  | 1st cycle | | Beginning of each subsequent cycle | Day 1 | Day 8 | Day  29 | Every 4 weeks thereafter |  | 1 year after starting protocol treatment | Every 3-6 months | 3 years after enrollment of last subject |
|  |  | Day 1 | Day 8 |  |  |  |  |  |  |  |  |  |
| Basic information / background | ● |  |  |  |  |  |  |  |  |  |  |  |
| PS | ● | ● | ● | ● | ● | ● | ● | ● | ● | ● |  |  |
| Compliance |  | ● | ● | ● | ● | ● | ● | ● | ● | ● |  |  |
| Clinical laboratory tests | ● | ● | ● | ●* | ● | ● | ● | ● | ● | ● |  |  |
| Signs and symptoms, adverse events | ● | ● | ● | ● | ● | ● | ● | ● | ● | ● |  |  |
| Tumor markers | ○ | ○ | ○ | ○ | ○ | ○ | ○ | ○ | ○ | ○ | ○ | ○ |
| Imaging or pathological tests | ○* (Every 3-6 months) | | | | | | | | | | | |
| Confirmation of relapse and secondary cancer | Confirmed as appropriate based on clinical symptoms, etc. | | | | | | | | | | | |
| Presence of therapy following protocol treatment |  |  |  |  |  |  |  |  |  | ● | ● | ● |
| Confirmation of outcome |  |  |  |  |  |  |  |  | ● | ● | ● | ● |

●: Must be done. ○: To be done when possible

●*: To ensure patient safety, it is desirable to perform clinical laboratory tests at times besides the beginning of each cycle.

○*: Diagnostic imaging or pathological tests will be performed every 3-6 months to confirm the presence of relapse or secondary cancer. However, appropriate tests will also be performed whenever relapse or secondary cancer is suspected.

†: Will be performed every 3-6 months, counting from the protocol treatment initiation day.

⋅ Reporting When reporting to the Data Center, data will be input according to the following schedule.

| Reporting time  Input sheet | Enrollment | Immediately after treatment initiation | Treatment period | | | | | | Follow-up |
| --- | --- | --- | --- | --- | --- | --- | --- | --- | --- |
|  |  |  | TS-1-treated arm | | | UFT-treated arm | | |  |

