12.3.2. Adverse events

Adverse events will be tabulated by treatment arm and type, and Fisher’s exact test will be used to compare AE incidences.

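### After Day 8 of cycle 1, scheduled TS-1 cycle-start laboratory tests follow 7 drug-free days while UFT tests fall on continuous drug, so laboratory adverse events are not ascertained alike for the comparison in 12.3.2

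*Protocol*

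**What the plan says.** - **Dosing.** Protocol 7.1.2 gives TS-1 "daily for 14 days (Day 1-14) with a 7 day rest period (Day 15-21"), repeated for one year. Section 7.1.1 gives UFT every day for one year with no planned break.
- **Test days.** Under 9.1.2, TS-1 subjects are tested on the first dosing day, then on "Day 8 of the first cycle and on the first day of the second and all subsequent cycles". UFT subjects are tested on the "first dosing day (Day 1), Day 8, and Day 29 during the first 4 weeks and then every 4 weeks".
- **Other required tests.** The 9.2 table also requires laboratory tests in both arms at the one-year completion visit and at discontinuation.
- **Extra tests.** A footnote in 9.2, attached only to the TS-1 column for later cycles, says "it is desirable to perform clinical laboratory tests at times besides the beginning of each cycle". It sets no days and makes no such test obligatory.
- **What is recorded.** Under 9.1.2, the forms keep the presence and highest grade of laboratory AEs.
- **How it is compared.** AEs are a secondary endpoint. Section 12.3.2 states that Fisher's "exact test will be used to compare AE incidences".
- **Rest rule.** Section 7.2.1 has the dosing criteria checked for TS-1 after the rest week and for UFT during treatment. It then sets one rule for both arms: if listed events "occur during the drug treatment period, drug treatment will be immediately withdrawn".

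**The concern.** A between-arm test of incidence assumes that events had a similar chance of being seen in each arm. For laboratory AEs that chance depends on when blood is drawn. A fall in neutrophils or platelets, or a rise in bilirubin, transaminases or creatinine, that appears in the two dosing weeks and recovers during the rest week can go unseen at a TS-1 cycle start. The same change on UFT is more open to detection, because the drug has not been paused before the draw.

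Three things depend on this:

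1. The laboratory part of a secondary endpoint. Section 2.4.1 chose the two-weeks-on, one-week-off schedule partly to limit adverse reactions, so a lower TS-1 laboratory rate would be readily believed.
2. The laboratory trigger of the rest rule, which is worded for events during dosing although the later TS-1 cycle-start tests are not drawn then.
3. The count of 25 subjects with treatment-related Grade 4 neutropenia in 17.2.1, which relies on the same detection. It is a stopping count, not a between-arm test.

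**Working it through.** **Check of the cycle count.** The protocol gives no figure for the laboratory comparison. The one figure that can be checked is that "about 18 cycles will be administered". Cycle starts fall on Day 1 + 21k. With 1 + 21k ≤ 365, k runs from 0 to 17, which gives 18 starts, the last on Day 358. The stated figure is reproduced.

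**Test days over 365 days, on-time schedule, no unplanned rest.**

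- TS-1: 18 cycle starts plus Day 8 of cycle 1 make 19 tests, or 18 after baseline. One of the 18 (Day 8) is on drug. The other 17 (Days 22, 43, … 358) each follow Days 15-21 of the previous cycle, that is, 7 drug-free days.
- UFT: Days 1 and 8, then 29 + 28k ≤ 365. Here k runs from 0 to 12, which gives 13 tests (Day 29 to Day 365). In total there are 15 tests, 14 of them after baseline, all on drug.

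| Scheduled tests | TS-1 | UFT |
|---|---|---|
| After baseline | 18 | 14 |
| On drug | 1 | 14 |
| On drug, after Day 8 | 0 of 17 | 13 of 13 |

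The completion and discontinuation visits come on top for TS-1. On this schedule Day 365 is Day 8 of cycle 18 (365 − 358 + 1 = 8), so the completion test is on drug. A discontinuation test is on drug only if that visit falls in a dosing period.

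**What timing could do to Fisher's test (illustration).** The documents give no laboratory AE incidence and no recovery time, so these inputs are assumptions. Take the planned 250 per arm, the same true incidence p in both arms, every affected UFT subject detected, and a fraction c of affected TS-1 subjects detected. Expected counts are 250p (UFT) and 250pc (TS-1), rounded.

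| p | Missed in TS-1 (1 − c) | TS-1 v UFT | Two-sided Fisher p |
|---|---|---|---|
| 30% | 25% | 56 v 75 | 0.067 |
| 30% | 33% | 50 v 75 | 0.013 |
| 30% | 50% | 38 v 75 | 0.0001 |
| 10% | 25% | 19 v 25 | 0.43 |
| 10% | 33% | 17 v 25 | 0.26 |
| 10% | 50% | 13 v 25 | 0.06 |

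Under the same assumptions, the exact probability that Fisher's test gives p < 0.05 although the true incidences are equal is:

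| p | c = 100% | 90% | 75% | 50% |
|---|---|---|---|---|
| 10% | 0.036 | 0.049 | 0.133 | 0.512 |
| 20% | 0.039 | 0.071 | 0.275 | 0.863 |
| 30% | 0.040 | 0.097 | 0.439 | 0.978 |

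**The loss is per subject, not per episode.** A subject is missed only if no test catches any of that subject's episodes. If half of all episodes recover unseen, independently, a subject with three episodes is missed with probability 0.5³ = 0.125. At 30% incidence that leaves 75 × 0.875 ≈ 66 v 75, p = 0.43.

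The effect therefore runs from negligible to decisive within plausible assumptions, and the documents do not say which applies.

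**The case against.** A reader might infer that the comparison is biased in favour of TS-1. The documents do not show that:

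- They give no nadir or recovery time.
- TS-1 has more scheduled post-baseline tests (18 v 14), which helps detection in that arm.
- UFT, tested every 4 weeks, can also miss transient events.
- Sites that follow the footnote add TS-1 tests with no UFT counterpart, which can push the imbalance the other way.
- The window of ±14 days from Week 4 permits some on-drug TS-1 draws.

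All of this stands against a stated direction or size. None of it restores comparability. Extra tests vary by site, the window requires no on-drug draw, and 7.2.1 still wants values confirmed before a TS-1 cycle starts.

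A reader might also infer that 7.2.1 cannot operate in the TS-1 arm. That goes too far. The section itself distinguishes when each arm is checked, and it says what to do if an event occurs without promising a test in every dosing period. Symptoms, investigator judgement and extra tests can still trigger it. What remains is that its laboratory trigger has little required on-drug input for TS-1.

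Nor is it right that TS-1 has no required on-drug test between Day 8 and one year, since the discontinuation visit can supply one.

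Finally, different calendars are natural when a cyclic regimen is compared with a continuous one. That is fair, but the comparison in 12.3.2 takes no account of it.

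**Conclusion.** The point holds as a difference in ascertainment. After Day 8 of cycle 1, on an on-time schedule, 17 of 17 scheduled TS-1 cycle-start tests follow a drug-free week and 13 of 13 UFT tests are on drug. Required on-drug TS-1 tests are then limited to the completion visit and any discontinuation visit that falls in a dosing period.

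Fisher's test on laboratory AE incidences can therefore show or hide a difference through test timing. The counts rest on on-time visits and uninterrupted dosing. The p-values above are illustrations under assumed incidence and detection, and do not estimate the bias in this trial.

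The reach is limited. The symptom AEs listed in 9.1.2 need no blood draw, and disease-free, relapse-free and overall survival are untouched. The change is worth making because it is cheap and prevents an unsupported claim of lower laboratory toxicity. It does not threaten the primary analysis.

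**What to change.** 1. **Treatment report.** Record the worst laboratory grade from scheduled tests separately from the worst grade from extra tests, each with its test date. Forms that keep only the highest grade per period cannot make this separation later.
2. **Section 12.3.2.** Base the between-arm laboratory AE table on scheduled tests and show extra-test results separately. Label results after Day 8 as after-rest (TS-1) and on-drug (UFT). Treat any p-value for laboratory AEs as descriptive, and make no claim of lower laboratory toxicity from it alone.
3. **Do not restrict the comparison to Days 1 and 8.** Those days are sampled alike, but Day 1 is essentially baseline. The restriction would leave about one week of a one-year treatment and discard cumulative toxicity.
4. **Sections 7.2.1, 9.1.2 and 9.2.** Reconcile the rest rule for the drug treatment period with the TS-1 test days and the footnote on extra tests. How this is done is for the clinical team.

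The cost is two added form fields and the loss of a confirmatory p-value for laboratory AEs. Items 1 and 2 need no extra visit or blood draw.

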# Adverse Event Evaluation and Reporting

8.1. Definition of adverse event

An adverse event (AE) is any undesirable medical event occurring in a subject receiving the protocol treatment. An AE does not necessarily have to show a definite causal relationship with the protocol treatment. Thus, an adverse event is any undesirable or unintended sign (including abnormal clinical laboratory values), symptom, or disease occurring when the protocol treatment is received regardless of the causal relationship to the protocol treatment.

An AE is a serious adverse event (SAE) if it is any of the following.

1. Death

2. Life-threatening

3. Admission to a hospital or clinic or prolongation of admission that is necessary for treatment

4. Disability/incapacity

5. An event that may result in disability/incapacity

6. Any other serious event consistent with 1-5.

7. Congenital diseases or abnormalities in subsequent generations

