8.2. Evaluation of adverse events

AEs observed during or within 30 days after completion of the protocol treatment will be evaluated according to the schedule in “9.2. Observation, test, and reporting schedule.” The maximum severity of each AE during each cycle will be recorded in the case report form.

The AEs observed will be evaluated according to the JCOG/JSCO Japanese-language version of the Common Terminology Criteria for Adverse Events (CTCAE) v.3.0. AEs will be graded according to the definitions (Grade 0-4) that most closely fit the event.

AEs for which a causal relationship to the drug cannot be ruled out will be considered adverse drug reactions.

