Symptom terminology: Fatigue (malaise), weight loss, rash/desquamation, hyperpigmentation, anorexia, diarrhea, mucositis/stomatitis, nausea, vomiting, other (Remarkable events will be recorded.)

Grade: The highest grade during each case report form preparation period will be recorded.

Causal relationship: Yes, No

Confirmation of relapse and secondary cancer

Diagnostic imaging or pathological tests will be performed to confirm the presence of relapse or secondary cancer every 3-6 months after initiation of the protocol treatment. However, appropriate tests will be performed whenever relapse or secondary cancer is suspected from clinical symptoms or the like.

Presence of relapse (If present, the following items will be entered in the outcome report.)

Relapse site: local, distant (brain, bone, lung, liver, lymph node, adrenal gland, skin, other)

Confirmation method and date confirmation performed: simple chest radiography, ultrasonography, CT, MRI, PET, histopathology, cytology, other

Confirmation date (If diagnosed by multiple diagnostic methods, the date the earliest test was performed.)

Presence of secondary cancer (If present, the following items will be entered in the outcome report.)

Site of occurrence of secondary cancer (head and neck, lung, esophagus, stomach, other)

Diagnostic method and date diagnosis performed: simple chest radiography, ultrasonography, CT, MRI, PET, histopathology, cytology, other

Date of diagnosis (If diagnosed by multiple diagnostic methods, the date the earliest test was performed.)

*The presence of relapse and secondary cancer will be confirmed in accordance with “Definition of relapse and secondary cancer” in 11.1.

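### Non-serious, non-laboratory adverse events outside the nine listed symptoms are recorded only if judged remarkable, so their between-arm Fisher tests rest on an undefined, unblinded judgement

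*Protocol*

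**What the plan says.** Section 8.1 defines adverse events broadly: "an adverse event is any undesirable or unintended sign (including abnormal clinical laboratory values), symptom, or disease occurring when the protocol treatment is received", whatever the causal relationship. Section 8.2 then sets a recording rule with no filter: "The maximum severity of each AE during each cycle will be recorded in the case report form".

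Section 9.1.2, which governs what sites observe and report during treatment, is narrower. It names nine symptoms (fatigue, weight loss, rash/desquamation, hyperpigmentation, anorexia, diarrhea, mucositis/stomatitis, nausea, vomiting) and closes with "other (Remarkable events will be recorded". Its recording unit also differs: "The highest grade during each case report form preparation period will be recorded". Separately, it has sites enter the presence and highest grade of adverse events for eight laboratory parameters (WBC, neutrophils, platelets, hemoglobin, total bilirubin, AST, ALT, creatinine). Section 9.1.4 sends serious adverse events to section 8.

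Adverse events are a secondary endpoint (Objective; section 11.2.3). Section 12.3.2 plans the analysis: "Adverse events will be tabulated by treatment arm and type, and Fisher’s exact test will be used to compare AE incidences". It does not separate systematically collected terms from the others. The schema states that the trial is open-label.

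**The concern.** A site cannot follow both recording rules. A Grade 1 unlisted symptom must be entered under 8.2 and may be left out under 9.1.2. The protocol gives no grade or other criterion for *remarkable*, so the choice falls to an investigator who knows the treatment. Section 2.4.1 tells that investigator that adverse drug reactions to TS-1 are numerous. The same event could be noted in one arm and passed over in the other.

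If that happened, Fisher's test for an unlisted event type would respond to recording habits as well as to toxicity. This is a data-capture rule. An event never entered cannot be recovered by a later statistical analysis plan, so the matter cannot simply be deferred to one.

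**Working it through.** **Scope of the filter**

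| Event class | Rule that applies | Subject to *remarkable*? |
|---|---|---|
| Nine named symptoms | 9.1.2, highest grade | No |
| Eight laboratory parameters | 9.1.2, presence and highest grade | No |
| Serious adverse events | 9.1.4, referring to section 8 | No |
| All other events | 9.1.2, last item of the symptom list | Yes |

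Only the last row is in question.

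**Recording unit.** Section 8.2 records by cycle. A cycle is defined only for TS-1 (7.1.2), while UFT is given daily without cycles (7.1.1). Section 9.1.2 uses the case report form period, which runs nearly in parallel: cycle 4 (12 weeks), cycle 8 (24 weeks) and 1 year for TS-1, against 3, 6 and 12 months for UFT. Whether a subject ever had an event, and its worst grade, are the same whichever unit is used. The mismatch does not change the incidences compared in 12.3.2.

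**Effect on Fisher's test.** The protocol gives no figure to reproduce here and no recording shares. The calculation below is an illustration.

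- From the protocol: 250 subjects per arm (section 10.1).
- Assumed: the same true incidence π in both arms, and recording shares r₁ and r₂.
- Recorded incidence in arm i is π × rᵢ. At π = 10% with shares of 80% and 65%, this is 0.10 × 0.80 = 8.0% and 0.10 × 0.65 = 6.5%, or 20 and 16.25 expected subjects out of 250.
- Rejection probability is the sum, over all pairs of counts (a, b), of Bin(a; 250, πr₁) × Bin(b; 250, πr₂), taken where the two-sided Fisher p-value is below 0.05.

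Exact enumeration gives:

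| True incidence | 80% vs 80% | 80% vs 65% | 80% vs 50% |
|---|---|---|---|
| 2% | 1.7% | 2.0% | 3.1% |
| 3% | 2.3% | 2.9% | 5.5% |
| 5% | 3.0% | 4.5% | 10% |
| 10% | 3.5% | 7.4% | 22% |
| 20% | 3.8% | 13% | 47% |

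Equal shares keep the error below 5% throughout, though recorded incidence is then 20% below the truth in both arms. At 80% versus 65%, the error stays below 5% up to a true incidence of 5% and exceeds it at 10%. At 80% versus 50%, it exceeds 5% from about 3%.

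**The case against.** The strongest reply is that much of this information is captured elsewhere. Under 7.2.1, any other adverse event of Grade 2 or higher meets the rest criteria in both arms. Under 7.2.2, Grade 3 or higher meets the dose reduction criteria. Section 9.1.2 lists the presence of and reason for rest, dose reduction and discontinuation among its data items. Many unlisted events of Grade 2 or higher should therefore leave a trace under a grade-based rule common to both arms. This largely stands, and it means that the fully discretionary remainder is mainly Grade 1. But a reason for rest is not a graded adverse event entry, and events during a scheduled TS-1 rest week may leave no such trace. Section 9.1.2 also limits web reporting to underlined items, and the underlining is lost in the text reviewed here. Which of these fields reach the Data Center cannot be established.

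A second reply is that unlisted events are likely to be uncommon, and at 2% to 5% incidence a moderate recording gap keeps the test below its nominal level. That stands too, as the table shows.

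A third reply is that the choice of terms to test belongs in the statistical analysis plan. That is fair for the list of tests, but not for what is entered in the case report form.

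**Conclusion.** Sections 8.2 and 9.1.2 contradict each other on which adverse events are recorded. For non-serious, non-laboratory events outside the nine symptoms, the comparison in 12.3.2 rests on an undefined judgement made by unblinded investigators. That much follows from the text alone.

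The size of any bias does not. It depends on recording shares and true incidences that the protocol does not give, and inflation becomes material only with a large recording gap or a true incidence of about 10% or more.

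A reader might infer more, and the document does not support it:

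- That the whole adverse event comparison is unreliable. The nine symptoms, eight laboratory parameters and serious events are outside the filter.
- That recording will differ by arm. Nothing shows this; the protocol only fails to prevent it.
- That the cycle wording in 8.2 invalidates the UFT data. It is a drafting mismatch that leaves subject-level incidence unchanged.

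Severity is minor. Disease-free, relapse-free and overall survival are not affected.

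**What to change.** - **Section 9.1.2:** replace the *remarkable* criterion with an objective recording threshold that is identical in both arms, for example all other adverse events of CTCAE Grade 2 or higher plus all serious adverse events. Sites already identify Grade 2 events in order to apply 7.2.1. The change concerns recording only.
- **Section 8.2:** restate which events are recorded so that it matches the threshold chosen in 9.1.2; otherwise the contradiction remains for Grade 1 events. Use the same unit, the highest grade per case report form period in both arms.
- **Section 12.3.2:** apply Fisher's exact test only to the nine symptoms and eight laboratory parameters, and list all other events descriptively by arm.

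The cost is some extra case report form entries, wording changes in three sections, and no p-value for unlisted events. Grading remains an unblinded judgement, as it already is for the nine symptoms, but it is made against published criteria.
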